### Oncologic results

Contralateral regional failures are defined as histopathologically proven contralateral recurrence in lymph node levels which were excluded from the ENI, as defined by the institutional guidelines. The regional control will be assessed during each follow-up visit of patients to the outpatient department. The evaluation of the neck will include US, and FNAC when indicated, every 3 months during the first year after treatment. Since most regional failures occur in the first year after treatment, the analysis for this endpoint will be started one year after the inclusion of the last patient. An overview of standard follow-up assessments is shown in Table 1.

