#### Primary endpoint

Cumulative incidence of contralateral regional metastasis at 1 and 2 years after treatment.

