### Pre-treatment evaluation

Standard pretreatment evaluation includes ultrasound of the neck and fine needle aspiration cytology (US-FNAC) performed by a dedicated head and neck radiologist, contrast-enhanced CT scan (and/or MRI), and FDG-PET (Table 1). During US, hypoechogenicity, round shape, border irregularity, a short axis greater than 5 mm, and loss of fatty hilus are considered signs of possible malignancy for which FNAC is performed to confirm or exclude lymph node metastasis. On MRI, a short axis > 10 mm, border irregularity with or without extension in adjacent structures and MRI signs of necrosis are considered signs of possible malignancy. On CT, a short axis > 10 mm, round shape, signs of necrosis, border irregularity with or without extension in adjacent structures are considered signs of possible malignancy. Only in case of a clinically negative neck on one side (N1-2b) or on both sides of the neck (N0), a patient is eligible for inclusion. After the initial work-up, a head and neck surgeon will assess the location and extent of the primary tumor during an investigation under general anesthesia, and will take a biopsy from the primary site.

**Table 1 Tab1:** Schedule of assessments

	Baseline	During RT	Follow-up					
			1st year^a^				2nd year^a^	3rd-5th year^a^
			12w^a^	6 m^a^	9 m^a^	12 m^a^	every 4 m	every 6 m
Standard of care:								
Physical examination	x	x	x	x	x	x	x	x
Flexible endoscopy	x		x	x	x	x	x	x
Toxicity	x	x	x	x	x	x	x	x
QoL-questionnaire	x		x	x	x	x	until 18th month^a^	
US-FNAC	x		x	x	x	x	when indicated	
CT or MRI^b^	x		x	when indicated				
FDG-PET	x		when indicated					
Investigation under anesthesia	x		when indicated					
RT planning CT	x							
Extra in SUSPECT-2:								
Signed informed consent	x							
Tracer injection and SPECT/CT	x							
Contralateral SNP	only when contralateral drainage is visualized on SPECT/CT							

^a^After end of radiotherapy

^b^According to our institutional guidelines, patients with oral cavity or oropharyngeal tumor are staged by MRI, while laryngeal and hypopharyngeal tumors are staged by CT

Abbreviations: *w* weeks, *m* months, *RT* radiotherapy, *US-FNAC* ultrasound-fine needle aspiration cytology, *SNP* sentinel node procedure

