### Sample size estimation

The probability of cRF in carefully selected patients with lateralized HNSCC was estimated to be 2% at 2-years [19–21]. The preliminary results of the proof-of-concept study, the SUSPECT 1, showed that after a median follow-up of 30 months only one patient (2%) developed cRF when treated to one side of the neck. With the inclusion criteria expanded to allow for lateralized T4 tumors, we estimated the rate of cRF to be around 5% or lower. The study was designed to demonstrate a cRF rate ≤ 15%. The limit of 15% is motivated by the fact that an elective irradiation of the neck in case of HNSCC is indicated only when the chance of occult metastasis in the neck exceeds 15% [22–24]. Approximately 90 evaluable patients are required (exact test for a binomial proportion with H0: *p* = 0.15, HA: *p* = 0.05, power = 0.80, α = 0.05, two-sided). Evaluable patients mean those who are treated unilaterally. Patients who are treated bilaterally (patients with contralateral micro−/macrometastases or those with a failed SPECT/CT) will be regarded as not evaluable for the primary and secondary end points and will be replaced by including new evaluable patients. The accrual period of the study is estimated to be 48 months, based on an inclusion rate of at least 2 patients per month.

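### The primary analysis starts one year after the last inclusion, when about a quarter to a third of patients cannot yet have the 2-year status named in the primary endpoint

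*Protocol article*

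**What the plan says.** The Primary endpoint section reads: "Cumulative incidence of contralateral regional metastasis at 1 and 2 years after treatment". The abstract gives the same two time points. In the schedule of assessments (Table 1), the follow-up columns carry the footnote "After end of radiotherapy", so follow-up time is counted from there.

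Oncologic results sets the start of the analysis by a different clock: "the analysis for this endpoint will be started one year after the inclusion of the last patient". The reason given is "Since most regional failures occur in the first year after treatment". The article states no other analysis date for this endpoint.

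Under Sample size estimation, "Approximately 90 evaluable patients are required", from an exact binomial test of 15% against 5% with 80% power and two-sided 5% significance. The first planning input there is a 2-year rate ("lateralized HNSCC was estimated to be 2% at 2-years"). On timing: "The accrual period of the study is estimated to be 48 months", "based on an inclusion rate of at least 2 patients per month". The Follow-up section continues visits to five years.

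**The concern.** The trigger runs from inclusion; the endpoint runs from treatment. Between the two lie lymph drainage mapping, planning and 35 fractions. A trigger of 12 months after the last inclusion therefore falls slightly short of the 1-year time point for the last patients and well short of the 2-year time point for everyone included in roughly the last year or more of accrual.

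That most failures come early is a reason to expect few late ones. It does not supply the missing 2-year status. An exact binomial test needs a yes or no for every patient at one fixed time. At the stated date the analyst must drop patients, treat unobserved time as failure-free, or test another time point, and the article does not say which. In a single-arm trial that withholds contralateral irradiation, any undercount of failures favours concluding that this is safe.

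**Working it through.** **The plan's own figure.** Exact lower-tail test at 0.025, n = 90, null 15%: reject with 6 or fewer failures. P(X ≤ 6 | 90, 0.15) = 0.0131 and power P(X ≤ 6 | 90, 0.05) = 0.836. The continuity-corrected normal approximation gives 88. The stated 90 is sound if all 90 have known status.

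**Inputs.**
- Accrual A: 48 months as stated, or 90 ÷ 2 = 45 months at the stated minimum rate. Uniform accrual is assumed.
- Lag L from inclusion to end of radiotherapy: not stated. Treatment alone takes 35 ÷ 5 = 7 weeks or 35 ÷ 6 = 5.8 weeks, about 1.5 months. With work-up and planning I assume 2 to 3 months, and show 0 as the lower bound.

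**Share without potential follow-up at the trigger.** Short of 2 years: (12 + L)/A. Short of 1 year: L/A.

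| L (months) | <2 y, A = 48 | <2 y, A = 45 | <1 y, of 90 (A = 48; 45) |
|---|---|---|---|
| 0 | 12/48 = 25.0% (22.5) | 12/45 = 26.7% (24) | 0; 0 |
| 1.5 | 28.1% (25.3) | 30.0% (27) | 2.8; 3 |
| 2 | 29.2% (26.2) | 31.1% (28) | 3.8; 4 |
| 3 | 31.2% (28.1) | 33.3% (30) | 5.6; 6 |

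(Patients of 90 in brackets.)

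**Route 1: test only patients with potential 2-year follow-up.** With A = 48 that leaves about 62 to 68 patients; with A = 45 and L = 3 it falls to 60. Exact power at lower tail ≤ 0.025:

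| n | Reject if ≤ | Power |
|---|---|---|
| 60 | 3 | 65% |
| 62 | 3 | 62% |
| 65 | 3 | 59% |
| 66 | 4 | 77% |
| 68 | 4 | 75% |

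Power moves in steps because the rejection limit is a whole number. Over 60 to 68 it stays between 59% and 77%.

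**Route 2: keep all 90 and count unobserved time as failure-free.** Assume a true 2-year risk of 0.15, a share f of failures in year 1, and failures spread evenly within each year. The average risk captured by the trigger is

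0.15 − 0.15(1 − f) × (12/A) × ½ − (L/A) × [0.15(1 − f) + 0.15 f × L/24].

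- A = 48, L = 2, f = 0.8: 0.15 − 0.00375 − 0.00167 = 0.1446; P(X ≤ 6) = 1.8%.
- A = 48, L = 3, f = 0.6: 0.15 − 0.0075 − 0.00445 = 0.1380; P(X ≤ 6) = 2.7%.

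With complete 2-year data the false-pass probability is 1.3%.

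**The case against.** Four points can be made for the plan.

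1. The endpoint is a cumulative incidence, and such an estimator uses censored patients. With A = 48 and L = 2 to 3, about 90% to 91% of the potential 2-year person-time is available at the trigger, before deaths and losses. This stands for estimation. It does not rescue the exact binomial test, and the article does not say how the two fit together.
2. The endpoint has two time points and the trigger nearly serves the first. Nothing says that this is the final analysis, follow-up goes on to year five, and a condensed article may leave a later 2-year read-out to the full protocol. This stands as mitigation, but the sentence as written covers the whole endpoint.
3. The timing is an open choice with a stated reason. That reason bears on the size of the bias, and Route 2 shows the bias to be small.
4. Only the 2% input carries a 2-year horizon. The 5% alternative and the 15% limit carry none. This also stands, and is why the time point of the test needs to be named.

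A reader might infer something stronger: that the 15% limit would be judged on 1-year status in all patients. If 80%, 70% or 60% of failures fell in year 1 and the true 2-year risk were 15%, the 1-year risks would be 12%, 10.5% and 9%, and P(X ≤ 6 | 90) would be 7%, 15% and 29%. The document does not support that reading. No section prescribes 1-year status for everyone, and at the stated date about 70% of patients would already have full potential 2-year follow-up.

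**Conclusion.** The inconsistency is real. The only stated analysis date cannot deliver complete 2-year status: about 25% to 33% of patients lack potential 2-year follow-up, or 29% to 31% with 48-month accrual and a 2 to 3 month lag. With that lag, about 4 to 6 of 90 also lack 1 year after radiotherapy. These shares rest on uniform accrual and an assumed lag. They concern potential follow-up; a patient who fails before the cut does have an outcome.

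The consequence depends on the route taken. Dropping the incomplete patients costs power (about 59% to 77% against the stated 80%). Counting them as failure-free shifts cRF slightly downward, with a false-pass probability of about 1.8% to 2.7% against 1.3%, for 60% to 80% of failures in year 1. That remains close to the 2.5% tail of the planned two-sided test. The sample size itself is not wrong. This is a timing conflict to resolve before results are seen, not a flaw that undermines the design.

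**What to change.** Amend the sentence in Oncologic results so that each time point has its own start, counted from the end of radiotherapy. The 1-year analysis starts when the last evaluable patient has reached 12 months after the end of radiotherapy, and the 2-year analysis when that patient has reached 24 months, or earlier cRF, death or loss in either case. In Sample size estimation, state which time point the test against 15% uses.

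Cost: the 2-year result comes 12 + L months after the present trigger, about 14 to 15 months for a lag of 2 to 3 months. If the 1-year rate is named as the tested endpoint, the main test moves only by the 2 to 3 month lag and the 2-year rate is reported later. Neither option adds visits, because standard follow-up already runs to five years.

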### Assessment of toxicity

Acute (≤90 days after start of treatment) and late toxicity will be evaluated by the radiation oncologist during the weekly visit of patients to our outpatient’s department, and during all follow-up visits afterwards. Toxicity scores will be collected using Common Terminology Criteria for Adverse Events version 5.0 (CTCAE).

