### Study objectives and endpoints

#### Objectives

To investigate the contralateral regional failure rate after radiotherapy (with or without cisplatin-based chemotherapy, cetuximab or immunotherapy) for patients with HNSCC nor crossing the midline, treated with SPECT/CT-guided unilateral ENI.To investigate the toxicity of this treatment strategy, and the impact on patients’ quality of life.To investigate the prevalence of tumorpositive contralateral sentinel nodes in patients with HNSCC not crossing the midline.

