### Side studies

The removed lymph nodes will be studied to determine the prevalence of occult metastatic disease in contralateral SNs. Additional information on the technical aspects of peritumoral injections in the outpatient clinic, the contralateral sentinel node procedure and lymphatic drainage patterns will be collected.

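### The toxicity objective covers the whole strategy, but the endpoint is limited to radiation-related toxicity, so complications of the added sentinel node procedure do not count as worded

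*Protocol article*

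**What the plan says.** The second item under Objectives is "To investigate the toxicity of this treatment strategy, and the impact on patients’ quality of life". The Secondary endpoint section and the Methods part of the abstract both restrict the matching endpoint to radiation-related toxicity.

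Under Assessment of toxicity, the scoring rule is "Acute (≤90 days after start of treatment) and late toxicity will be evaluated by the radiation oncologist during the weekly visit of patients", extended by "and during all follow-up visits afterwards". On the instrument it says "Toxicity scores will be collected using Common Terminology Criteria for Adverse Events version 5.0 (CTCAE").

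Table 1 ticks toxicity at baseline, during radiotherapy and in every follow-up column. It lists tracer injection with SPECT/CT, and the contralateral sentinel node procedure, as extras of this study; the procedure is done "only when contralateral drainage is visualized on SPECT/CT". According to the abstract, it takes place on the day of the tracer injection.

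Side studies adds "Additional information on the technical aspects of peritumoral injections in the outpatient clinic, the contralateral sentinel node procedure" and drainage patterns as further information to be collected. It does not name complications.

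**The concern.** The contralateral sentinel node procedure is what this study adds to the concept of the first SUSPECT study (Background). It is done so that more patients can be spared bilateral irradiation, and the case for the trial is lower toxicity and better quality of life. If the toxicity result counts only radiation-related events, it shows the benefit of the smaller irradiated volume and leaves out any harm from the surgery used to select patients for it. The objective, read literally, asks for both.

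A second question is timing. The procedure comes before radiotherapy, whereas the acute window and the weekly visits belong to the treatment period. Whether a short-lived surgical complication meets any listed scoring point depends on when baseline is scored, and the article does not say.

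**Working it through.** There is no stated figure to reproduce. The check sets the sections side by side and then sizes the group concerned.

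**Step 1: scope.**

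| Item | Section | Scope |
|---|---|---|
| Objective | Objectives | Toxicity of the treatment strategy |
| Endpoint | Secondary endpoint; abstract, Methods | Radiation-related toxicity, early and late |
| Acute window | Assessment of toxicity | Up to 90 days from start of treatment |
| Strategy components | Abstract, Interventions, Table 1 | Tracer injection, SPECT/CT, conditional sentinel node procedure, then radiotherapy |

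A complication of the node procedure belongs to the strategy but is not radiation-related. It falls within the objective and outside the endpoint, even if a clinician sees and grades it.

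**Step 2: order of events.** The pathology result of the procedure decides whether the contralateral neck is irradiated (Treatment: radiotherapy regimens), so the procedure must precede radiotherapy. I read the start of treatment as the start of radiotherapy, because scoring is assigned to the radiation oncologist at the weekly visits.

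**Step 3: listed scoring points.** The only toxicity tick in Table 1 before radiotherapy is in the baseline column. That column also holds the tracer injection, and no order within it is given. There are two cases:

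- Baseline before the procedure: a complication that has resolved before radiotherapy has no listed scoring point. One that persists can be graded at the weekly or follow-up visits, as a change from baseline.
- Baseline after the procedure: a scoring point exists, but a complication present then becomes part of the reference value for toxicity, and for quality of life if the EORTC forms are completed at the same time.

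The two cases exclude each other in any one patient, and the article establishes neither.

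**Step 4: size of the group.** Inputs: about 90 evaluable patients (Sample size estimation); contralateral drainage in about 20% of patients in the first SUSPECT study; contralateral sentinel nodes in 8–40% of patients in the sentinel node studies cited (Background). Formula: patients with the procedure = 90 × share.

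- 90 × 0.20 = 18
- 90 × 0.08 = 7.2, about 7
- 90 × 0.40 = 36

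These are patients who would have the procedure, not patients harmed or left unscored. The article gives no complication rate, so the effect on the toxicity result cannot be calculated.

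**The case against.** The strongest reply is that the endpoint is a coherent choice. The rationale throughout is the radiation toxicity of bilateral against unilateral treatment, and the Discussion part of the abstract states the aim in those terms. Only the wording of the objective is broader, so it could be narrowed. That is a legitimate way to remove the contradiction, but the trial would then not answer the question its objective now poses.

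A reader might go further and infer that surgical complications fall outside every visit and that toxicity is scored only once treatment has started. The documents do not support this. Table 1 ticks toxicity at baseline, and CTCAE scoring at the later visits is not limited to items attributed to radiation, so a persisting complication can be graded. The 90-day rule separates acute from late toxicity; it does not say that earlier events are ignored. The Side studies sentence can be read as collecting information on the node procedure generally, not only on its technical aspects.

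It is also tempting to state that the strategy's toxicity is understated, or that change from baseline is biased in its favour. Both depend on facts that the article does not give: a complication rate, and the order of baseline and procedure.

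Finally, this is a condensed article. Adverse event reporting is commonly left to the full protocol, and the detailed description of the node procedure was not available for this check. Absence of surgical safety reporting therefore cannot be claimed. What remains is that separate adverse event reporting would not by itself bring these events into an endpoint worded as radiation-related.

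**Conclusion.** The mismatch between objective and endpoint stands on the article's own wording. Complications of the contralateral sentinel node procedure do not count in the toxicity endpoint as worded, although the procedure is part of the strategy whose toxicity is to be investigated. If baseline is scored before the procedure, a complication that resolves before radiotherapy may also have no listed scoring point. The toxicity of the strategy may therefore be understated.

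The group concerned is a minority: about 18 of 90 patients, range 7 to 36. This assumes that the drainage shares in the Background apply to this trial's wider inclusion criteria and to its evaluable patients. The size of any understatement is unknown. The conclusion concerns what the endpoint counts, not whether complications are recorded anywhere. The change is worth making because it is cheap and the trial's case rests on toxicity.

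**What to change.** 1. Define the secondary endpoint as toxicity of the treatment strategy, with CTCAE v5.0 events counted from tracer injection onward. Report procedure-related events (tracer injection, sentinel node procedure) separately from radiation-related events, so that the radiation result stays readable on its own. Use the same definition in the abstract, Secondary endpoint and Assessment of toxicity.
2. Record events since the procedure at a contact that already takes place before radiotherapy, such as the planning CT, or at the first weekly visit, and add the tick to Table 1.
3. State in Table 1 that baseline toxicity and the EORTC forms are completed before tracer injection and the sentinel node procedure.

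If the sponsor prefers to keep the endpoint as it is, the objective should be narrowed to match, with a statement that complications of the node procedure are outside it.

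The cost is a protocol amendment and one extra case report form page; no new visit is needed. The downside is a slightly less favourable toxicity figure for the strategy.

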### Quality of life assessment

Quality of life (QoL) will be assessed at baseline, and 3, 6, 12, and 18 months after treatment, using the European Organization for Research and Treatment of Cancer Quality-of Life-Questionnaire-C30 (EORTC QLQ-C30) and the European Organization for Research and Treatment of Cancer Quality-of-Life Questionnaire-Head and Neck 35 (EORTC QLQ-HN35). These questionnaires are a standard part of the follow-up visits in our institution and as such represent no additional burden to patients.

### Response evaluation

The response evaluation will be done according to the institutional guidelines 12 weeks after treatment by physical examination of the neck and primary tumor site, including flexible endoscopy. MRI (for oral cavity and oropharyngeal cancer) or contrast-enhanced CT scan (for laryngeal and hypopharyngeal cancer) will be performed to assess the response at the primary site and US-FNAC to assess the nodal state after treatment. In case of doubt about complete response to the primary treatment, FDG-PET followed by examination under general anaesthesia will be done.

### Follow-up

Subsequently, oncologic follow-up visits are scheduled at 6, 9 and 12 months during the first year after RT (including an additional US-FNAC at each visit), every four months in the second year after RT and every 6 months in the third to fifth year after RT (including US-FNAC only when indicated). After five years patients will be discharged from follow-up if there is no evidence of disease. This follow-up schedule is identical to the standard follow-up schedule for HNSCC patients in our institution.

### Sample size estimation

The probability of cRF in carefully selected patients with lateralized HNSCC was estimated to be 2% at 2-years [19–21]. The preliminary results of the proof-of-concept study, the SUSPECT 1, showed that after a median follow-up of 30 months only one patient (2%) developed cRF when treated to one side of the neck. With the inclusion criteria expanded to allow for lateralized T4 tumors, we estimated the rate of cRF to be around 5% or lower. The study was designed to demonstrate a cRF rate ≤ 15%. The limit of 15% is motivated by the fact that an elective irradiation of the neck in case of HNSCC is indicated only when the chance of occult metastasis in the neck exceeds 15% [22–24]. Approximately 90 evaluable patients are required (exact test for a binomial proportion with H0: *p* = 0.15, HA: *p* = 0.05, power = 0.80, α = 0.05, two-sided). Evaluable patients mean those who are treated unilaterally. Patients who are treated bilaterally (patients with contralateral micro−/macrometastases or those with a failed SPECT/CT) will be regarded as not evaluable for the primary and secondary end points and will be replaced by including new evaluable patients. The accrual period of the study is estimated to be 48 months, based on an inclusion rate of at least 2 patients per month.

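### The single 15% test names neither of the endpoint's two time points, and the planned analysis date does not fit the 2-year one

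*Protocol article*

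**What the plan says.** All references are to the protocol article.

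- **Primary endpoint** (and the Abstract): a cumulative incidence of contralateral regional metastasis "at 1 and 2 years after treatment". Two time points are named and neither is ranked above the other. The footnote to Table 1 counts follow-up from the end of radiotherapy.
- **Sample size estimation**: one test is specified, an "exact test for a binomial proportion with H0", with "H0: *p* = 0.15, HA: *p* = 0.05" and "power = 0.80, α = 0.05, two-sided". From this, "Approximately 90 evaluable patients are required". Neither the limit nor the alternative is dated: "we estimated the rate of cRF to be around 5% or lower" gives no horizon. The only dated rate tied to a fixed horizon there is the 2% background figure at 2 years.
- **Same section, denominator**: "Evaluable patients mean those who are treated unilaterally". No minimum follow-up is required. Replacement is described only for patients treated bilaterally.
- **Oncologic results**: the analysis of this endpoint begins one year after the last patient is included, on the ground that most regional failures come in the first year.

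**The concern.** The article states the endpoint, test, limit, error rate, power, denominator and analysis date, and these stated parts do not fit together. The 2% background rate points to a 2-year test. The analysis date and its reasoning point to a 1-year test. The test itself is for a simple proportion, while the endpoint is a time-based quantity that some patients will not have reached at the cut.

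Two consequences follow. First, a cumulative incidence cannot fall with time, so the 1-year reading is never the harder one to pass. If the choice is left open, the 15% limit can be claimed at whichever point passes. Second, a simple proportion applied literally to everyone treated unilaterally would treat patients still short of 24 months as if their 2-year status were known.

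Both work in favour of declaring safety. This is a single-arm trial of omitting contralateral irradiation, and the Discussion hopes its results will widen the use of unilateral treatment.

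**Working it through.** **Inputs from the article:** p0 = 0.15, p1 = 0.05, two-sided α = 0.05 (0.025 in the lower tail), power 0.80, n about 90, accrual 48 months, analysis 12 months after the last inclusion.

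**Assumptions, not in the article:** even accrual; radiotherapy (RT) ends 0 to 2.5 months after inclusion; a share s of the failures by 2 years falls in year 1, with failures spread evenly within each year.

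**1. The plan's own figure.** The normal approximation gives n = [(1.96·√(0.15·0.85) + 0.842·√(0.05·0.95)) / 0.10]² = 78.0. With continuity correction, (78.0/4)·[1 + √(1 + 2/(78.0·0.10))]² = 87.7, so about 90 is reproduced. For the exact test at n = 90:

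- P(X ≤ 6 | 0.15) = 0.0131 and P(X ≤ 7 | 0.15) = 0.0308, so the rule is 6 or fewer failures.
- Power is P(X ≤ 6 | 0.05) = 0.836.

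The number is adequate if every patient's status at the tested time is known.

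**2. Follow-up at the planned cut.** Time since inclusion is uniform from 12 to 60 months.

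- Under 24 months from inclusion: 12/48 = 25%, or 22.5 of 90.
- Under 24 months from the end of RT, if RT ends 2.5 months after inclusion: (12 + 2.5)/48 = 30.2%, or 27.2 of 90.
- Under 12 months from the end of RT, on the same assumption: 2.5/48 = 5.2%, or 4.7 of 90.

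**3. Raw proportion with administrative censoring only, true 2-year rate 15%.** Patients with 12–24 months of follow-up miss on average half of their year-2 failures.

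- Clock from inclusion: p = 0.15·[s + (1 − s)(1 − 0.25·0.5)].
- Clock from the end of RT: the 5.2% with under 12 months miss all year-2 failures and on average 1.25/12 = 0.104 of year-1 failures. So p = 0.15·[s(1 − 0.052·0.104) + (1 − s)(1 − 0.125 − 0.052)].

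| Clock | s | Observed p | P(X ≤ 6) |
|---|---|---|---|
| Inclusion | 0.8 | 0.146 | 1.7% |
| Inclusion | 0.6 | 0.143 | 2.1% |
| End of RT | 0.8 | 0.144 | 1.9% |
| End of RT | 0.6 | 0.139 | 2.6% |

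The slack in the exact rule (1.3% against 2.5%) absorbs almost all of this.

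**4. The limit read at 1 year when the true 2-year rate is 15%.** The 1-year rate is 0.15·s.

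| s | 1-year rate | P(X ≤ 6 of 90) |
|---|---|---|
| 0.9 | 0.135 | 3.2% |
| 0.8 | 0.120 | 7.4% |
| 0.7 | 0.105 | 15.4% |
| 0.6 | 0.090 | 28.9% |

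**The case against.** The strongest reply is that the binomial test appears only in the sample-size paragraph, that the named endpoint is a cumulative incidence, and that the handling of censoring and death normally belongs to the full protocol or SAP, which are not shown. Much of this stands, and it rules out several stronger readings.

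- **A reader might infer that the plan scores dead and unobserved patients as failure-free.** The article does not say so. It would follow only from applying the stated test literally to the stated denominator.
- **A reader might infer that deaths bias the rate downward.** For the stated endpoint they do not. With death as a competing event, a patient who dies without cRF is a non-event, and with complete follow-up that estimate equals the raw proportion. A death-free risk is a different quantity. The reasoning behind the 15% limit, as a chance of occult neck disease, makes that risk worth reporting, but it does not justify a second pass criterion.
- **A reader might infer that the test as planned is clearly too lenient.** From the incompleteness built into the schedule, the effect is about 1.7–2.6%. A larger excess needs sizeable further loss: 5% of patients wholly unobserved but kept as failure-free gives 2.1%, 10% gives 3.2% and 20% gives 7.4%. The article gives no loss rate.
- **A reader might take 3–29% as a type I error.** It is not. If the null is 15% at 1 year, the error at 1 year is 1.3%. The range shows only what a 1-year pass is worth as evidence about 2 years.

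The missing time point is not answered by this reply. An article that prints the hypotheses, error rate, power and analysis date has stated the decision rule, and as stated it is compatible with either of two different claims.

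**Conclusion.** The point holds as an inconsistency between the endpoint, the test and the analysis date, and it should be settled before the analysis. The main weakness is the undated limit: a 1-year pass could be presented as meeting the 15% limit when the 2-year rate is 15%, with a probability of about 3–29% depending on the assumed timing of failures. The mismatch between a raw proportion and a partly followed cohort is secondary and small on the plan's own schedule. The follow-up counts rest on even accrual, and the upper count also on RT ending about 2.5 months after inclusion. The sample size itself is sound: 83.6% exact power at n = 90 with complete 24-month data.

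**What to change.** Under **Sample size estimation**, state that:

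- the 15% limit is tested once, at 24 months after the end of RT;
- the 12-month estimate is supportive and carries no pass/fail claim;
- success means that the upper limit of the two-sided 95% confidence interval for the 24-month cumulative incidence is below 15%, with incomplete follow-up censored and death without cRF as a competing event.

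Name the interval method as well, because it can move the rule by one event. With complete data on 90 patients, a log-log interval on the failure-free proportion has an upper limit of 14.2% at 6 failures and 15.6% at 7, so the rule stays at 6. A log-log interval on the failure proportion gives 14.5% at 7 and would allow 7, with a lower-tail error of 3.1%.

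Under **Oncologic results**, align the analysis date with the 24-month time point. A death-censored estimate can be reported as a sensitivity analysis.

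**Cost.** The number of patients does not change. Full 24-month follow-up moves the decisive analysis by 24 − 12 = 12 months if counted from inclusion, or 24 + 2.5 − 12 = 14.5 months if RT ends 2.5 months after inclusion. If the present date is kept, the 24-month estimate is somewhat less precise, and the 83.6% power, which assumes complete data, no longer applies exactly. In either case the reported rate will be slightly less favourable than a raw proportion at the current cut.
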